### Objectives {7}

The main objective is to compare differences in microscotomas between the “active peeling of the ILM” group and the “no ILM peeling” group between the inclusion visit and 6 months after surgery. The main criterion is the difference between the number of microscotomas (sensitivity < 10 dB).

The secondary objectives are the difference of anatomical and functional changes of the retina between the two groups at 1, 6, and 12 months and the rate of recurrence of ERM at 12 months. Various endpoints are assessed: VA measurements (ETDRS scale) and near vision (Parinaud); microperimetry; questionnaires of visual discomfort; and SD-OCT analysis.

An ancillary study is also conducted and concerns the patients who undergo spontaneous peeling of the ILM during the surgery, as they cannot be included in the main study. The aim is to compare primary and secondary endpoints between patients with spontaneous peeling and patients in the active peeling group at inclusion visit and 1, 6, and 12 months after surgery.

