#### Sample size {14}

A retrospective study conducted in the Department of Ophthalmology of the University Hospital of Nantes in 2013 [23] showed that of 11 patients who received active peeling, the number of microscotomas was 2.5 ± 3.1 preoperatively and 6.5 ± 7.3 at 1 month.

Based on the number of microscotomas found in the active peeling group in our retrospective study, with 80% power and a type I error of 5%, 100 patients are needed to highlight a halving of the number of microscotomas in the non-peeling group relative to the active peeling group (i.e. 6 ± 6 microscotomas average peeling in the active group compared to 3 ± 4.6 in the non-peeling group).

Usually, only very few patients do not attend their 6-month visit. However, the occurrence of EIGs (endophthalmitis, retinal detachment) may prevent the determination of the number of microscotomas at 6 months by microperimetry. Assuming that at most 5% of patients will be affected, 106 patients will be randomized, or 53 patients per group.

As all the patients with spontaneous peeling during surgery will not be randomized, > 106 have to be enrolled. The estimated number of spontaneous peeling was initially 30% [23], so the number of patients enrolled were thought to be 156. During the study, we noted that spontaneous peeling occurred in 50.2% of cases and so the number of patients to enroll in the study has been revised to 222 patients (amendment to the protocol in December 2017).

The ability of the six centers to recruit is estimated to be 120 patients per year (30 patients per center), given that the primitive ERM is a common disease.

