### Assignment of interventions: allocation

#### Sequence generation {16a}

Randomization will be conducted openly and stratified by center. It will be performed according to a 1:1 ratio and balanced by blocks. The software used for the randomization is SAS version 9.4.

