#### Plan to promote participant retention and complete {18b}

In our current practice, we have noticed that very few patients refuse to attend the visit at 6 months that corresponds to the visit of the main objective (Fig. 1). A letter to remind them of the follow-up visit is sent 2 months before it. However, in case of no show or of serious adverse event (SAE; endophthalmitis, including retinal detachment), missing values for the primary endpoint will be dealt with multiple imputation*.* For the secondary endpoints, there will be no attribution of missing data.

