### Statistical methods

#### Statistical methods for primary and secondary outcomes {20a}

The variables measured at baseline are described for all patients in both group by numbers and percentages for each category for categorical variables and the minimum, maximum, average, standard deviation, and quartiles for the quantitative variables.

The primary endpoint is the difference between the number of microscotomas measured before surgery and the number of microscotomas measured at 6 months (a number in the range of 0–29). The mean difference is calculated in each of the two groups and compared using a mixed linear regression model to take into account the stratification of the randomization of the center (the center will be considered as a random effect) and adjustment for the preoperative number of microscotomas. Then, center-effect is analyzed with a fixed-effect model.

The following secondary endpoints are analyzed using a mixed linear regression model: comparison of the number of microscotomas in the two groups between preoperative visit and at 12 months; description and comparison of the type of microscotomas before surgery and at 1, 6, and 12 months; comparison of changes in mean visual acuity and in mean retinal sensitivity; study of the association between the presence of SANFL or DONFL with the number of microscotomas; comparison of the OCT B scan; and study of the associations between data in the OCT B scan and VA and between data in the OCT B scan and the presence of microscotomas.

The comparison between the two groups in the frequency of symptoms (blurred vision, metamorphopsia, relative scotoma, diplopia and micropsia), the comparison of the percentage of abnormalities detectable by OCT in front of the layer of optical fibers, and the comparison of the percentage of recurrence of the ERM at 12 months between the two groups are analyzed by Chi-square tests stratified on the center.

The correlation between VA and retinal sensitivity (the central point and the average of the five most central points) are analyzed according to the measurement of Pearson or Spearman’s correlation coefficients.

In addition, a description for each group of the number of microscotomas that are not located in a gripping area of the ERM and the ILM (at 1 month and 6 months) and a description of the outcome (disappearance/persistence) of microscotomas that existed before the surgery at 1 and 6 months is done.

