#### Methods in analysis to handle protocol non-adherence and any statistical methods to handle missing data {20c}

As already stated very few patients generally refuse to attend the visit at 6 months. However, for the primary endpoint, in case of no show or of SAE (endophthalmitis, including retinal detachment), missing values will be dealt with multiple imputation.

Secondary endpoints: there will be no attribution of missing data for the secondary endpoints.

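### The microscotoma count is imputed at month 6 but not at month 12, and the month-12 analysis is not stated to use the earlier visits: a cheap improvement of low severity

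*Protocol article*

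**What the plan says.** All references are to the protocol article.

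- **Missing data.** Section {20c} assigns multiple imputation to the primary endpoint and then states that "there will be no attribution of missing data for the secondary endpoints". Section {18b} repeats the rule: "For the secondary endpoints, there will be no attribution of missing data".
- **Month 12.** Section {20a} lists, among the secondary endpoints analysed by mixed linear regression, "comparison of the number of microscotomas in the two groups between preoperative visit and at 12 months".
- **Model structure.** The same section gives the primary model a random centre effect and adjustment for the preoperative count. It names no patient effect, visit term or arm-by-visit term for any endpoint.
- **Month 1.** Section {20a} compares the type of microscotoma at months 1, 6 and 12. It compares the number at month 6 (primary) and month 12 (secondary) only. Section {7} sets as a secondary objective "the difference of anatomical and functional changes of the retina between the two groups at 1, 6, and 12 months".
- **Data available.** Table 2 schedules microperimetry at inclusion and at months 1, 6 and 12.
- **Expected loss.** Section {14} allows for loss at month 6 only: "Assuming that at most 5% of patients will be affected, 106 patients will be randomized, or 53 patients per group". No figure is given for month 12.

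**The concern.** The same count, from the same test, is treated differently at two adjacent visits. The reasons given for imputing at month 6 (missed visits and serious adverse events that prevent microperimetry) apply equally at month 12. If the month-12 model uses only the preoperative and month-12 tests, a patient who misses month 12 contributes nothing, even with month-1 and month-6 counts on file.

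Two consequences follow. Month 6 would represent all randomized patients through imputation, and month 12 only those who attended. And if patients with many microscotomas at month 6 attend month 12 less often, the month-12 difference shrinks and may be read as recovery. The article's rationale is lasting visual discomfort, so readers will look to month 12 to see whether a month-6 difference persists.

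There is also a small mismatch between objectives and analysis. The number at month 1 has no listed between-group comparison, although month 1 is the postoperative time point of the pilot count in section {14}.

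**Working it through.** **1. The plan's own figure.** Section {14} states that "with 80% power and a type I error of 5%, 100 patients are needed", for "6 ± 6 microscotomas average peeling in the active group compared to 3 ± 4.6 in the non-peeling group". Section {16a} gives the allocation: "It will be performed according to a 1:1 ratio and balanced by blocks".

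- SD = √[(6² + 4.6²)/2] = √28.58 = 5.346
- n per arm = 2 × [5.346 × (1.960 + 0.842)/3]² = 49.85, so 50 per arm and 100 in total (two-sided; a one-sided test would need 80)
- 100/0.95 = 105.3, so 106 randomized

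The stated sample size reproduces and is not in question.

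**2. Power at month 12, random loss.** Assumptions: the planning difference (3) and SD carry over to month 12; month 6 is complete; the correlation ρ between months 6 and 12 is 0.3 to 0.9; d is the month-12 loss.

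- Complete cases: n = 53(1 − d) per arm; power = Φ[3/(5.346√(2/n)) − 1.96]
- Joint model: effective n = 1/[(1 − ρ²)/(53(1 − d)) + ρ²/53]
- Example, d = 5%, ρ = 0.7: 1/[0.51/50.35 + 0.49/53] = 51.6, against 50.35 for complete cases

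| Month-12 loss | Complete cases | Joint, ρ 0.3 to 0.9 |
|---|---|---|
| 5% | 80.4% | 80.6% to 82.0% |
| 10% | 78.2% | 78.6% to 81.6% |
| 15% | 75.9% | 76.5% to 81.1% |
| 20% | 73.4% | 74.1% to 80.6% |

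The largest gain is 1.6 points at 5% loss and 7.2 points at 20%.

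**3. Bias when loss depends on the month-6 count.** Simulation with 4,000 runs per setting and 53 per arm. Assumptions: true difference 3, SD 6 and 4.6, correlation 0.7 between postoperative visits and 0.4 with baseline, and odds ratio for missing month 12 of 2.7 per SD of the month-6 count. Counts are treated as normal. Complete-case ANCOVA is set against an analysis that predicts missing month-12 values from arm, baseline, month 1 and month 6.

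| Loss | Complete-case difference | Shortfall | Joint difference |
|---|---|---|---|
| 5% | 2.853 | (3 − 2.853)/3 = 4.9% | 3.008 |
| 10% | 2.728 | 9.1% | 2.985 |
| 14% | 2.645 | 11.8% | 3.003 |

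With completely random loss neither method is biased. The standard errors are 0.976 and 0.961 at 5% (0.961/0.976 = 0.985, 1.5% smaller), 1.005 and 0.976 at 10% (2.9% smaller), and 1.035 and 0.994 at 15% (4.0% smaller).

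**4. Sensitivity to the mechanism.** Suppose that only active-peeling patients with high month-6 counts tend to be lost, with ρ 0.5 to 0.7. Moderate dependence gives a complete-case difference of about 2.9 at 5% loss and 2.55 to 2.7 at 20%. As an extreme bound, if exactly the worst patients leave, it is 2.5 to 2.7 at 5% and 1.5 to 2.0 at 20%.

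**The case against.** The strongest reply is that the text does not describe a single-visit analysis. It says mixed linear regression without giving its structure for secondary endpoints. The centre effect is named in the paragraph on the primary endpoint, and covariance details commonly sit in an analysis plan that is not shown. A likelihood-based model over visits would use every observed test without imputing anything, so it agrees with the no-imputation rule. This stands: a reader might infer that the plan certainly throws away the earlier visits, or has no handling of missing values, and the document supports neither. What it supports is that imputation is ruled out and that nothing stated brings months 1 and 6 into the month-12 comparison.

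A reader might also infer that month 1 is not compared at all. That is too broad. The type of microscotoma is compared at month 1, and section {12} lists mean retinal sensitivity at months 1, 6 and 12. Only the number lacks a listed comparison.

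It is fair, too, that the loss, correlations and mechanism are assumed. The article names missed visits and serious adverse events as causes of missing tests, not a high month-6 count. Where an adverse event already prevents the month-6 test, there is little to borrow. At 5%, the only loss figure in the document, the shift is about 0.15 microscotoma.

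Finally, imputing only the primary endpoint is a common choice. That is a reason for low severity. It does not remove the inconsistency for one outcome measured repeatedly.

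**Conclusion.** The point holds as a low-severity improvement. The imputation rule differs between months 6 and 12 for the same count. As worded, the month-12 comparison leaves out patients without that test, and the number at month 1 is not compared despite the stated objective.

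At 5% loss the effect is small: a difference about 5% too small if loss depends on the month-6 count, or a standard error about 1.5% larger than necessary if loss is random. It reaches 9% to 12% bias at 10% to 14% informative loss, and would matter more if month-12 loss were both larger and strongly informative. All of this rests on an assumed month-12 loss, assumed correlations and an assumed mechanism.

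It would be wrong to conclude that the trial's main result is compromised. The primary analysis and the 106 randomized patients are untouched, and month 12 is one secondary endpoint among several.

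**What to change.** Analyse the microscotoma count, and mean retinal sensitivity, at months 1, 6 and 12 in one likelihood-based repeated-measures model with arm-by-visit terms, the preoperative value, centre and an unstructured within-patient covariance. Report the month-1 and month-12 differences from it. This needs no imputation, so the rule for secondary endpoints can stay. Alternatively, extend the imputation planned for month 6 to the month-1 and month-12 counts, with the counts at the other visits in the imputation model. If a joint model was already intended, one sentence saying so settles the point.

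The cost is a few lines of analysis-plan text and a slightly longer program; no new data are needed. The result relies on data being missing at random, which standard imputation at month 6 already assumes. Patients whose adverse event already prevents the month-6 test gain little.

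The month-6 primary analysis stays as specified.

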#### Plans to give access to the full protocol, participant level-data, and statistical code {31c}

According to French law, the results of the study will be published on the website of the regulatory authority. However, data sharing is prohibited by the General Data Protection Regulation European law.

### Oversight and monitoring

#### Composition of the coordinating center and trial steering committee {5d}

It has been possible to carry out the protocol and the trial thanks to an Executive Committee which includes a Scientific Committee and a Steering Committee. The Scientific Committee was created and the project manager of the clinical investigation center (CIC1413). The Steering Committee is composed of the members of the Scientific Committee with the addition of the data management team, the nurse study who coordinates assistance for patient inclusion in the other centers, and the monitoring CRA. The sponsor project manager coordinates this committee and drafts the “PEELING newsletter”, which provides, among other things, the latest news on patient inclusion, amendments to the protocol, etc.

#### Composition of the data monitoring, its role, and reporting structure {21a}

This surgery is done in routine practice; therefore, a Data and Safety Monitoring Committee was irrelevant.

#### Adverse event reporting and harms {22}

Expected AEs as a result of epiretinal membrane and cataract surgery (according to the Société Française d’Ophtalmologie, www.sfo.asso.fr) are:
endophthalmitis (eye infection) (1–3 in 1000)changes in the macula, tear(s) of the retina, retinal detachment (3%) that may occur after surgery and require additional treatment by reoperation and/or laserclouding of the corneacentral retinal edemaretinal burn from the illumination of the surgical microscopeinadequately sealed scarpartial collapse of the upper eyelidsubconjunctival hemorrhage or of eyelidperception of floatersincreased sensitivity to lightinflammation of the eyeincreased intra-ocular pressure

All SAEs, whether expected or unexpected, require the completion of a SAE report. The investigator should verify that all the information noted in this report is precise and clear (no abbreviations, etc.).

All the surgery-related AEs occurring inside the operating room must be reported in the eCRF and, if they meet a seriousness criterion, transmitted to the sponsor.

Because they could be a risk of adverse drug reaction, any inadequacy or malfunction of a medical device or surgical equipment has to be notified to the sponsor as well as any misuse or error.

SAEs should be reported immediately (within 24 h of the investigator becoming aware of the event) to the sponsor by fax (Research Department, CHU de Nantes – Fax number: [name]).

On receipt of an unexpected SAE report, the sponsor should report it to the regulatory authorities. Once a year, the sponsor draws up an annual safety report.

In the event of SAEs involving discontinuing from the study or SAEs ongoing at the end of the study, the patient should be subject to follow-up until the SAE is resolved.

#### Frequency and plans for auditing trial conduct {23}

An inspection or audit may take place as part of this study, performed by the sponsor and/or by the regulatory authorities. Inspectors will check the documents, logistics, records, and any other resources that the authorities consider to be associated with the clinical trial and that may be located at the trial site itself.

#### Plans for communicating important protocol amendments to relevant parties (e.g. trial participants, ethical committees) {25}

The amended protocol will be a dated, updated version. If necessary, the information form and consent form should be amended. The sponsor project manager will notify the centers and a copy of the revised protocol will be sent to all the principal investigators to add to the Investigator Site File. Currently, the updated protocol is at version 7 on 6 February 2020. All the submissions/declarations were made by the Sponsor Department at CHU Nantes to the French regulatory authority (ANSM) and the ethic committee (Comité de Protection des Personnes OUEST IV – Nantes). The CRA of the Sponsor Department will report any deviations of the protocol. They will be fully documented using a breach report form.

#### Disseminations plans {31a}

The trial results will be published in international ophthalmological, medical, and scientific journals and presented at national and international conferences.

## Discussion

The peeling of the ILM is frequently practiced by surgeons during ERM surgery to reduce recurrences of ERM. It does not impair nor improve postoperative VA, but it increases the surgical risks and causes anatomical damages. This procedure may cause definitive visual discomfort which patients often complain about.

PEELING is designed to explore this aspect by comparing the difference in number of microscotomas whether the patients had their ILM peeled or not. The intention is to assess the benefit/risk ratio of ILM peeling. Recurrence of ERM, VA, patient’s visual discomfort, and various anatomical endpoints of the retina are also evaluated.

After receiving appropriate approval, the study included its first patient in September 2014. The study is conducted for 72 months; inclusions will stop as of September 2020. This recruitment period had to be extended as a result of more spontaneous peeling of the ILM during surgery compared to the proportion that was statistically planned.

This study is a single-blind trial considering the impossibility of blinding the surgeon during the practice of the ILM peeling. However, to limit any more bias, the follow-up visits are conducted by blinded ophthalmologists and orthoptists who do not know what action has been carried out.

Two features are particularly original in this study: randomization in the operating room and microperimetry as the primary endpoint.

On the one hand, randomization in the operating room fits with the everyday pratice when the surgeon has removed ERM and is assessing remaining ILM. It allows the prospective measurement of the “spontaneous peeling” rate and it generates a large group of > 100 patients included in the ancillary study. The comparisons of this group with the two groups—“active peeling” and “no peeling”—will elucidate the clinical significance of this phenomenon that has been largely neglected.

On the other hand, choosing microperimetry as the primary endpoint is unusual but crucial. It is justified by the fact that no study has yet shown that ILM peeling modifies postoperative VA but many studies have demonstrated anatomical damages. Visual outcome can not be limited to VA and more refined tests are needed to evaluate if these anatomical damages and associated with visual impairment. Deltour et al. [23] showed in a retrospective study that active ILM peeling is associated with more microscotomas than spontaneous peeling. This preliminary result has to be verified by a prospective randomized clinical trial.

With this study, the expected individual benefit is an improved visual comfort of patients operated for idiopathic ERM. If this study shows that active ILM peeling is significantly associated with more microscotomas and patient discomfort, it may contraindicate the ILM peeling during primitive idiopathic ERM surgery.

### Trial status

This trial is still ongoing; patient inclusion is not yet complete.

The updated protocol is at version 7 on 6 February 2020.

The first patient was included on 9 September 2014.

Recruitment by the investigating centers is planned to continue until September 2020.

## Data Availability

Data sharing is not applicable to this paper as no datasets were generated or analyzed during the current study. The investigators will share the entirety of the final trial dataset. Data collected during the test may be processed electronically, in accordance with the requirements of the CNIL (compliance with reference methodology MR001).

## Abbreviations

AE: Adverse event
AMD: Age-related macular degeneration
ANSM: Agence Nationale de Sécurité du Médicament et des produits de santé – French regulatory authorities
CNIL: Commission Nationale de l’Informatique et des Libertés – French National Commission on Informatics and Liberty
CRA: Clinical Research Associate
CRF: Case report form
DONFL: Dissociation of optic nerve fiber layer
ERM: Epiretinal membrane
ILM: Internal limiting membrane
OCT: Optical coherence tomography
SD-OCT: Spectral domain optical coherence tomography
SAE: Serious adverse event
SANFL: Swelling of the arcuate nerve fiber layer
SLO: Scanning laser ophthalmoscope
